## Discussion

Occupational rehabilitation programs are complex and are provided in unpredictable, open contexts, which may result in differences in achieved outcomes and variation in effects between subgroups of patients [10]. Mixed-method research draws upon the strength of both quantitative and qualitative approaches and is seen as a powerful tool for investigating complex processes and outcomes in health services research [73]. Combining these methods increases our possibility of understanding “what works” and why [74]. A process evaluation is seen as imperative for understanding the context of the participants, the setting, and the processes in which the results occur to make informed judgments about programs and their applicability to different settings and under different conditions [75]. Pragmatic approaches are also valued since they focus on real-world applications of interventions and are seen as better suited to provide a foundation for informed decisions among alternative treatments for patients, clinicians, and third-party funders [76].

There is still too little knowledge of the effectiveness and cost-effectiveness of inpatient and outpatient occupational rehabilitation programs for RTW among employees on sickness absences due to MSDs and CMDs.

### Strengths of the study

This study is one of the very few studies in Norway to investigate the results of occupational rehabilitation programs on RTW for patients with MSDs, CMDs, or unspecific problems. The longitudinal follow-up and a mixed-method approach with the use of registry data, questionnaires, and process evaluation are strengths of the study. The use of national registry data will eliminate recall bias and increase the quality and reliability of the data on the primary outcome. The use of qualitative data may open ‘the black box’ of the interventions and allow the description of how the clinicians, the patients, and the different stakeholders think the intervention might have worked and which mechanisms might have contributed to the results. Since both the selected patient groups and the delivery of the two programs are as close to normal practice as possible, the external validity of the results is also expected to be strengthened. Additionally, the broad approach of using different research questions and selecting methods with both explanatory and exploratory aims may generate new insight and understanding regarding the content, delivery, and reception of occupational rehabilitation programs; the RTW process; and ‘what works’ and why.

### Limitations of the study

A design with a randomized clinical trial is the preferred design to examine the study questions. This project started as a randomized clinical trial, but due to recruitment problems, it was not feasible to carry through. We stopped recruiting when we had reached approximately 80 participants and decided to change the design. These two randomized arms will be analyzed and reported separately as a pilot study. We do not have enough power in the statistical analyzes to evaluate whether there are any significant differences in effect between the two interventions.

With the two nonrandomized arms described in this article, we will not be able to evaluate whether there are any significant differences in effect between the two interventions, and we will not be able to eliminate the bias associated with differences in the referral of patients to the two clinics. However, interviews with nearly 40 participants, 4 times during a year from the randomized part of the study, will support us with valuable information regarding their reception of the interventions and mechanisms that influence their RTW process.

We know from interviews with participants that there is a bias associated with the referral of patients to the clinics due to patient preferences and possibilities. Some prefer the outpatient program because they can ensure their ability to fulfill family or work obligations or because they are not able to stay away from home for several weeks. On the other hand, some prefer the inpatient program because they can disconnect from family or work for a period.

Those who agree to participate in the study and those who decline may also differ in many unpredictable ways that we are not able to address with the current study design. However, we will look for any selection bias by comparing the demographic statistics and known predictors of RTW among those who agree to participate. The RTW rates in the study will also be compared with national RTW data from an established quality registry for occupational rehabilitation. We also plan to draw a matched group from the NAV registry representing those who receive treatment as usual and to compare RTW rates for this group with the results from the participating clinics.

The study intends to reveal whether there is a difference between the clinics regarding success in RTW rates for different patient groups. When multiple subgroup analyses are performed, the probability of a false-positive finding can be substantial, but when properly planned, reported, and interpreted, they can provide valuable information [77].

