## Methods/design

### Aims

This study will compare the results of two occupational rehabilitation programs in Norway for employees on sick leave due to MSDs, CMDs, and combined and unspecific conditions. In keeping with the aims of a pragmatic design, the selected outcomes are chosen to be relevant to practice [48]. In this setting, relevant stakeholders are physicians, NAV consultants, patients, practitioners, and clinicians who deliver occupational rehabilitation services. The intention is to inform decisions regarding the selection of efficient and cost-effective interventions that help people RTW and decisions regarding for whom an intervention is beneficial and in which circumstances. The selection of secondary outcomes is intended to identify modifiable factors that clinicians may target in their interventions to increase RTW rates among their patients [31, 36]. Another aim is to study the experience of collaboration between stakeholders to support RTW outcomes.

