The primary aim of the study is to evaluate whether there are any differences between the studied programs in the RTW success rates of the participating patients. Since both rehabilitation programs are complex and comprehensive, we hypothesize that there will be no overall differences in RTW rates but that some subgroups might benefit more from one or the other program. As earlier research has identified, there might be differences among subgroups based on gender; age; socioeconomic status; health complexity or severity; length of sick leave; job satisfaction; RTW expectations; the risk of job loss; and work-related strains such as demanding jobs, low decision latitude, conflicts, and poor support.Differences in cost-effectiveness will be evaluated if the programs show differences in RTW rates.The second aim of the study is to evaluate whether there are any differences between the programs in improvements in known modifiable obstacles to RTW, such as health and function, work ability, RTW expectations, RTW self-efficacy, and fear avoidance, among the participants.The third aim of the study is to examine the delivery and reception of the programs to understand how the interventions produce change. This aim will be achieved by investigating the clinicians’ evaluations of how the programs might work; the participants’ expectations of the program and how they respond to and interact with the interventions; and the effect of contextual factors on intervention mechanisms and outcomes in the RTW process, both at the individual and organizational levels.The fourth aim of the study is to explore key stakeholder views and experiences of RTW coordination. Key stakeholders are defined as patients, rehabilitation teams, employers, insurance case managers, general practitioners, and occupational health services.Our last two aims are to increase our understanding of any differences and similarities in the success of RTW outcomes for the participating clinics by combining the quantitative results for the primary objective of the study with the qualitative and quantitative results from the process evaluation in the study. An overarching aim is to support interactive learning between researchers and rehabilitation professionals for the development of program structures and practices that improve RTW outcomes for their patients.

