#### Secondary outcome measures

*Economic evaluation measures:* An economic evaluation will be performed if there is a statistically significant difference in RTW rates between the programs. The main outcome measure will be the incremental costs for an averted sick leave day in the two intervention groups compared to the reference group and in the inpatient program compared to the outpatient program. Data will be collected both through the administration of questionnaires and the extraction of records directly from the clinics. Health economic data will be collected 1 year after the participants’ initiation into the project. Subgroup analyses will also eventually be conducted.

A cost-utility analysis (CUA) will be performed by using a health-related quality of life questionnaire, the SF-12 version 2 [56], and converting the SF-12 scores to SF-6D scores. The SF-12 consists of 12 questions scored on 3- and 5-point Likert scales.

*Work ability:* Work ability will be measured with three items from the Work Ability Index (WAI) [57]. The participants will estimate their current work ability compared with their lifetime best ability. The score ranges from zero (cannot work at all) to ten (best work ability ever). The experienced work ability related to physical and psychological demands is scored on 5-point Likert scales. Work ability will be measured at all time points.

*Return-to-work self-efficacy (RTWSE):* RTWSE will be measured by the *Return-to-Work Self-Efficacy Scale* (RTWSE-19) [58, 59], which has three subscales: *meeting job demands* [7]*, modifying job tasks* [7] and *communicating needs to coworkers and supervisors* [5]. All items are scored on 10-point Likert scales.

*Fear avoidance for work:* Fear avoidance will be measured with a subscale from the *Fear-Avoidance Belief Questionnaire* [60, 61]. The scale consists of seven items and is scored on a 7-point Likert scale.

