#### Sample size

Estimation of the sample size is based on the assumption that approximately 50% of the patients will have a stable RTW, full-time or part-time, after 1 year. A two-sided survival analysis with a 5% level of statistical significance and 80% power shows that we will be able to detect a statistically significant difference between the programs at a hazard ratio of 0,73 with a sample size of 600 participants. Due to the lower capacity at the outpatient clinic, 200 participants will be recruited from the outpatient clinic and 400 will be recruited from the inpatient clinic.

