### Impact of the study findings

The study aims to inform general practitioners, NAV consultants, and occupational rehabilitation professionals about ‘what works’ and for whom interventions work in occupational rehabilitation, increasing their ability to make informed decisions in the selection of treatment and to develop interventions. With the use of a pragmatic approach and a process evaluation alongside the trial, the transferability of knowledge and possibilities for implementing effective approaches in the network of occupational rehabilitation clinics also increase.

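### The limitations section rules out evaluating a difference in effect between the two programs, yet the subgroup, economic and guidance plans need one, and nothing says how a significant result is to be read

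*Protocol article*

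**What the plan says.** **Limitations of the study.** The project began as a randomised trial, which stopped recruiting at about 80 participants and will be reported separately as a pilot. Of the two nonrandomised arms in this article the section says "we will not be able to evaluate whether there are any significant differences in effect between the two interventions". It also concedes that bias from the way patients reach each clinic will remain. It reports from participant interviews that patients' preferences and practical possibilities, such as family and work obligations or whether they can stay away from home, influence which clinic they are referred to.

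**Aims.** "The primary aim of the study is to evaluate whether there are any differences between the studied programs in the RTW success rates". The overall hypothesis is no difference, but some subgroups are expected possibly to benefit more from one program. The stated purpose includes informing "decisions regarding for whom an intervention is beneficial and in which circumstances".

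**Sample size.** "A two-sided survival analysis with a 5% level of statistical significance and 80% power" is said to show that "we will be able to detect a statistically significant difference between the programs at a hazard ratio of 0,73" with 600 participants, 200 outpatient and 400 inpatient.

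**Subgroup analyses.** Treatment-by-subgroup interactions are tested at the 5% level.

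**Secondary outcome measures; Cost-effectiveness/utility/benefit analyses.** An economic evaluation follows only if RTW rates differ significantly between the programs. "The main outcome measure will be the incremental costs for an averted sick leave day in the two intervention groups", compared with a reference group and with each other. The incremental cost-effectiveness ratio divides the cost difference by the difference in RTW outcomes.

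**Outcome assessment and evaluation.** Clinic differences in RTW are adjusted for a prognostic factor if it is imbalanced, if it is strongly correlated with RTW, and if power suffices.

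**Impact of the study findings.** Results are meant to tell referrers "for whom interventions work in occupational rehabilitation" and to support treatment selection.

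**The concern.** The limitations section does more than urge caution. It says that a difference in effect cannot be evaluated. An averted sick leave day, a subgroup that benefits more and advice on which program to choose all presuppose a difference that the programs caused. The article has no rule that carries the limitation into the reading of a significant hazard ratio, a significant interaction or the cost ratio.

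The economic analysis is the sharpest case. It starts when a test is significant, and that test may be unadjusted because adjustment depends partly on available power. A significant result produced by referral alone would therefore set off a cost per averted day for a difference that the article says it cannot attribute to the programs. Referrers and payers would receive effect-type figures from one part of the report and a disclaimer from another.

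**Working it through.** **1. Which statements need an attributable effect?**

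| Section | Planned statement | Can it be descriptive? |
|---|---|---|
| Aims (primary aim) | Difference in RTW success rates | Yes, but the article does not say so |
| Sample size | Significant difference between programs at HR 0.73 | Yes, but the article does not say so |
| Aims (subgroup hypothesis) | Some subgroups may benefit more | No |
| Subgroup analyses | Treatment-by-subgroup interaction at 5% | Only if benefit is not concluded from it |
| Secondary outcome measures; cost-effectiveness section | Cost per averted day; incremental ratio | No |
| Aims (purpose); Impact | For whom a program is beneficial or works | No |

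The first two rows can stand beside the limitation once they are labelled. The others conflict with it as written.

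**2. The article's own figure.** Inputs from Sample size: N = 600, about 50% with stable RTW at one year (about 300 events), 200:400, HR 0.73, two-sided 5%. By the Schoenfeld formula the information is 300 × (1/3) × (2/3) = 66.67, so SE(log HR) = 1/√66.67 = 0.1225. Power = Φ(|ln 0.73|/0.1225 − 1.96) = Φ(2.57 − 1.96) = 73%, against the stated 80%. If 50% is instead the slower arm's rate and that arm is the 400-patient one, Freedman's formula gives N = 606. So 600 is optimistic on the plain reading but not shown to be wrong, and the present point does not depend on it.

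**3. Threshold for significance.** exp(−1.96 × 0.1225) = 0.787. This is the HR closest to 1 that reaches p<0.05 with 300 events. Time to RTW is followed for five years, so later events would move the threshold nearer to 1.

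**4. Strength of an unmeasured factor that could explain it (E-value, common outcome).** RR ≈ (1 − 0.5^√HR)/(1 − 0.5^√(1/HR)); E = 1/RR + √[(1/RR)(1/RR − 1)].
- HR 0.787: RR = 0.847, E = 1.64.
- HR 0.73: RR = 0.804, E = 1.79.

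A factor associated with both clinic and RTW by a risk ratio of this size could account for the whole observed HR.

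**5. Chance of a significant result with no program effect.** Assumptions (the article gives none of these values): a referral factor is present in 40% of patients at one clinic and 15% at the other, it multiplies the RTW hazard by h, and there is no adjustment. Bias HR = (1 + 0.40(h − 1))/(1 + 0.15(h − 1)); d = ln(bias HR)/0.1225; P(p<0.05) = Φ(d − 1.96) + Φ(−d − 1.96).
- h = 1.5: bias HR = 1.200/1.075 = 1.116; d = 0.898; P = 14.6%.
- h = 2: bias HR = 1.40/1.15 = 1.217; d = 1.606; P = 36.2%.

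The bias formula holds exactly only at time zero. A simulation of the same example with a Cox model (600 patients, about 300 events, censoring at one year) gives HRs of 1.11 to 1.20 and rejection in 13% to 33% of studies, depending on h and on which clinic has the factor more often.

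Without specifying a factor, an assumed residual bias HR of 0.95, 0.90, 0.85 or 0.80 gives about 7%, 14%, 26% or 45%, against the nominal 5%.

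**The case against.** The strongest reply is that an observational study may properly detect a difference between clinics without attributing it to the programs. The primary aim speaks of RTW success rates and the power sentence of a difference between programs; neither uses a causal word. The overall hypothesis is no difference, the subgroup statement is tentative, and the economic analysis is conditional. This stands. A reader might infer that every planned element asserts a program effect and that the primary aim and power statement cannot coexist with the limitation. The text does not support that.

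The article also does not ignore bias. It names the referral mechanisms, plans adjustment, collects many prognostic variables at baseline and registry data from two years before inclusion, and plans comparison with a matched group from the NAV registry and with a national quality registry. To infer that the comparison is simply unadjusted would therefore also go too far. Even so, the adjustment is conditional on power and is not tied to the economic trigger, and neither external comparison says how the between-program result is to be interpreted.

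Finally, the E-values would apply to any observational HR of this size, and the prevalences and hazard multipliers are the reviewer's. That is correct. They show scale only.

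**Conclusion.** The point holds in limited form. The flat statement that effects cannot be evaluated conflicts with the subgroup-benefit hypothesis, with interaction tests read as benefit, with the cost per averted day and the incremental ratio, and with the guidance on what works for whom. The primary aim and power statement are ambiguous, not contradictory. The conflict lies within the printed text, so it is not detail left to an analysis plan.

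On size: with about 300 events at 1:2, an HR of about 0.79 suffices for significance. Under the assumed referral factor, roughly 15% to 36% of studies with no program effect would open the economic analysis, slightly fewer (13% to 33%) with attenuation. This assumes 300 events, no adjustment for the factor, and the HR as the RTW measure that sets the trigger. A reader might take these percentages as the study's actual false-positive rate. They are not, because the article gives no strength for the referral bias.

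**What to change.** 1. In Aims and Sample size, state the primary comparison as a confounder-adjusted comparison of RTW between patients attending the two clinics, interpretable as a program effect only if no important referral factor is unmeasured. Use that wording in place of the flat disclaimer in Limitations and of the effect wording in Aims and Impact.
2. Base both the economic trigger and the cost per averted day on adjusted differences, using the baseline prognostic variables and pre-inclusion registry data already planned. Drop the condition that adjustment depends on sufficient power, and label the economic results with the same interpretive condition.

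Optionally, give an E-value or similar tipping-point figure beside the primary HR.

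The cost is rewording in five or six sections, slightly more analysis and more modest claims. No new data are needed.

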### Impact of the study findings

The study aims to inform general practitioners, NAV consultants, and occupational rehabilitation professionals about ‘what works’ and for whom interventions work in occupational rehabilitation, increasing their ability to make informed decisions in the selection of treatment and to develop interventions. With the use of a pragmatic approach and a process evaluation alongside the trial, the transferability of knowledge and possibilities for implementing effective approaches in the network of occupational rehabilitation clinics also increase.

## Data Availability

The datasets generated during the current study will be available upon request from [name], [contact]. The participants will provide their consent to participate in the STAiR study but not to share their data with other parties. We expect that all data from questionnaires, registry data, and interviews will be available in 2027. To obtain the data, researchers must present research project approval from a Norwegian Regional Committee for Medical and Health Research Ethics or others. To obtain registry data on sick leave, a separate application must be sent to the Norwegian work and welfare administration. Anonymous data can be obtained by communication with the corresponding author.

## Appendix

**Table 3 Tab3:** Overview of questionnaire items and timing

Assessments	T0	T1	T2	T3
**Individual factors**				
Gender, age, education, marital status, children, demanding caregiver tasks, family economy, life events	X			
Work and benefit status	X	X	X	X
Changes in work and benefit status since start of rehabilitation			X	X
Subjective health complaints (SHC)	X			
SF-12	X	X	X	X
Health and illness perceptions, cause of complaints	X			
Physical activity	X		X	
**Work-related factors**				
Profession, Employment, hours of employment, working time arrangement, work tenure, type of employment (private/public, permanent/temporary), size enterprise	X			
Experienced downsizing, concerns about the job	X			
Accomodations at the workplace	X			
Employer/Colleagues respect functional ability	X			
Expected/plans for work/ work tasks after rehabilitation	X	X		
Job involvement, work commitment	X			
Work ability	X	X	X	X
Effort, reward imbalance (ERI)	X			
Work autonomy, support, conflicts (QPS Nordic)	X			
Organizational support	X			
Job satisfaction	X			
Planning change of employer	X		X	X
FABQ-Work	X	X		
RTW self-efficacy	X	X		
Important factors for RTW (21 items)		X		
RTW expectation	X	X	X	X
**Health Services**				
Evaluation of rehabilitation; improvement health and function		X	X	
Evaluation of rehabilitation; change in self-understanding, increased self-efficacy, motivation for change; improvement work ability, rehabilitation team; program components, collaboration stakeholders		X		
Use of health services	X		X	X

T0 = Enrollment; T1 = End of rehabilitation program; T2 = 6 months; T3 = 12 months

**Table 4 Tab4:** Overview of outcome assesments

	T0	T1	T2	T3	T4	T5
